## Discussion

### Principal Findings

This study protocol presents an outline of the first adaptive intervention trial designed to determine the efficacy of various support intensities (ie, none, low, and high) of a dMH treatment program for anxiety and depression. The primary objective is to compare the efficacy of clinical outcomes (anxiety and depression) among the 3 treatment conditions. Specifically, it is predicted that therapist assistance delivered via video chat will be more effective in reducing anxiety and depression symptoms compared with program-only support. If this hypothesis is supported by the study findings, it will demonstrate that augmenting a dMH intervention with therapist assistance offered via video chat is beneficial for enhancing mental health outcomes within a community mental health treatment setting. The difference between low and high therapist assistance will also be evaluated. If the results indicate that the outcomes of these treatment conditions are similar, support will be provided for the implementation of low-intensity dMH interventions within the community, thus increasing timely community access to evidence-based interventions.

The study also has several secondary objectives that will be assessed. Examination of the role of motivation; self-efficacy; and participant preferences in engagement, adherence, and clinical outcomes among the 3 treatment conditions will be beneficial in improving our understanding of factors affecting participant attrition and engagement within dMH interventions. Qualitative evaluation of participant and therapist experiences and satisfaction with video chat technology is expected to provide further knowledge about the use of video chat for the assessment and treatment of anxiety and depression, specifically, the development of therapeutic relationships, implementation barriers and facilitators, and strengths and limitations of video chat technology. Furthermore, qualitative exploration of therapist training and implementation experiences in the delivery of dMH interventions is likely to improve the future adoption of dMH interventions incorporating video chat technology.

The findings of the trial have the potential to contribute toward the evidence base of adaptive treatment designs for anxiety and depression, with considerable implications for the implementation of stepped care models in dMH. As the study will evaluate outcomes of health resources and health status among the 3 treatment conditions, it is anticipated that the study results will enhance our understanding of participant needs and resources required at the self-help (dMH program only; step 1) and therapist-assisted (low and high therapist assistance; step 2) levels in the context of an adaptive intervention design.

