### Sample Size Calculation

Only aggregate data will be used for the main analysis. Assuming a conservative medium effect (ie, GPower f[v] test=0.25), significance set at 5% (*P*=.05), and power at 80%, 98 cases are required to demonstrate statistical significance in the primary outcome measures. However, allowing for a 30% attrition rate [26], a total target sample size of 137 participants will be required.

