## Results

Recruitment began in November 2020 and was completed at the end of March 2022. In total, 240 individuals registered for the clinical trial, of which 113 (47.1%) were assessed as eligible to commence the dMH intervention. At week 3, of the 113 participants, 73 (64.6%) met the stepped care criteria to have the dMH intervention augmented with therapist assistance, whereas 40 (35.4%) remained in the program-only condition. The results of the clinical trial are forthcoming as they have recently been accepted for publication in JMIR Publications [27].

Data will be entered, screened, and analyzed using statistical software. Intention-to-treat analysis will be used for primary outcomes, controlling for baseline differences where appropriate. The primary analysis will be conducted using 2 planned contrasts comparing a change in anxiety (GAD-7) and depression (PHQ-9) scores from preintervention assessment with those of the postintervention (week 9) and follow-up (week 21) assessments, using a mixed model repeated-measure analysis. A mixed model repeated-measure analysis is preferred owing to its ability to include participants with missing data. The study will also investigate whether reliable and clinically significant change has been achieved for participants following the recommendations of Jacobson and Traux [28]. Moderation analyses will be used to determine the role of self-efficacy and motivation in engagement and adherence and their effects on anxiety and depression outcomes in the 3 treatment conditions, and a *t* test will be used to determine the impact of preferences and treatment allocations on attrition rates.

Data obtained from open-ended questions about intervention satisfaction questionnaires and from interview questions will be transcribed verbatim from audio recordings into text and then analyzed using protocols of thematic analysis to identify common themes. Text transcripts will be read several times to identify emerging themes. Thematic analysis allows for the identification of themes that are driven by the data, using an experiential, bottom-up approach [29]. Close analysis of the data will suggest names for the themes, which are likely to represent something of meaning to participants and therapists, with direct quotes used to further illustrate meaning. Researchers will meet throughout the analysis process to review and discuss the data.

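### Similar low- and high-intensity outcomes are to count as support for low intensity, but similarity has no criterion and the low-versus-high contrast is too imprecise to show it by default

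*Protocol article*

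**What the plan says.** Under Principal Findings, the protocol article says that low and high therapist assistance will be compared, and then gives the consequence of one possible result: "If the results indicate that the outcomes of these treatment conditions are similar, support will be provided for the implementation of low-intensity dMH interventions".

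The Sample Size Calculation section gives the only basis for the size of the trial: "Assuming a conservative medium effect (ie, GPower f[v] test=0.25", 5% significance, and "power at 80%, 98 cases are required to demonstrate statistical significance in the primary outcome measures". It continues: "allowing for a 30% attrition rate [26], a total target sample size of 137 participants will be required".

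The analysis text, placed under Results, says: "The primary analysis will be conducted using 2 planned contrasts comparing a change in anxiety (GAD-7) and depression (PHQ-9) scores". These use a mixed model for repeated measures, with intention to treat, at weeks 9 and 21. The two contrasts are not defined.

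The Randomization section allocates only between low and high intensity, at the point where a participant meets the step-up criteria. The Results section gives the number who reached that point: "At week 3, of the 113 participants, 73 (64.6%) met the stepped care criteria".

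**The concern.** A planned conclusion about services is tied to a finding of similarity, and the article gives no way to establish similarity. It states no equivalence or non-inferiority hypothesis, no margin and no confidence-interval rule. What it does fix is a test for a difference. A reader who applies that test to the low-versus-high contrast and finds nothing significant has no other criterion to hand, and could take the result as the similarity that the Discussion has in mind.

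Low versus high is also the only randomised comparison in the trial, so it is the one best able to carry a causal claim. It uses only the stepped-up subset. If that subset is too small to separate the arms reliably, imprecision could be reported as support for the less intensive option.

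**Working it through.** **Inputs from the article.** f(V) = 0.25, 5% significance, 80% power, N = 98, 30% attrition, target 137 (Sample Size Calculation); 73 of 113 met the step-up criteria (Results); block randomisation between low and high (Randomization).

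**Assumptions, not in the article.** 1:1 allocation, so 37 and 36; 30% attrition applied to this subset, 73 × 0.7 ≈ 51, so 26 and 25; two-sided 5% test; true difference of 0.5 SD, with 0.3 SD as a second value; correlation r between baseline and outcome from 0 (no adjustment) to 0.7.

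**Step 1: the plan's own figure.** For a multivariate repeated-measures group-by-time interaction with 3 groups and 3 time points, s = 2, df1 = 4 and λ = N·s·f² = 98 × 2 × 0.0625 = 12.25. Power is 80.05% at N = 98, so 98 reproduces. The 3 × 3 layout is inferred from three conditions and weeks 0, 9 and 21; a few repeated-measures layouts come within two or three of 98. A two-group one-way comparison at f = 0.25, which is d = 0.5, needs 128. On the closest match, then, 98 sizes an overall three-group effect and not the low-versus-high contrast. (98/0.7 is 140, not 137; the gap does not matter here.)

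**Step 2: chance of a non-significant result.** Two-sample noncentral t with noncentrality δ = (d/√(1−r²)) / √(1/n₁+1/n₂). The root term is √(1/37+1/36) = 0.234 and √(1/26+1/25) = 0.280.

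**Step 3: precision.** 95% half-width in SD units = t₀.₉₇₅ × √(1/n₁+1/n₂) × √(1−r²). For example, 1.994 × 0.234 × 1 = 0.467, and 2.010 × 0.280 × 1 = 0.563.

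| Analysed | r | δ at d = 0.5 | Power | Non-significant | Half-width (SD) |
|---|---|---|---|---|---|
| 37/36 | 0 | 2.136 | 0.558 | 44% | 0.47 |
| 37/36 | 0.4 | 2.330 | 0.633 | 37% | 0.43 |
| 37/36 | 0.6 | 2.670 | 0.750 | 25% | 0.37 |
| 37/36 | 0.7 | 2.991 | 0.839 | 16% | 0.33 |
| 26/25 | 0 | 1.785 | 0.417 | 58% | 0.56 |
| 26/25 | 0.4 | 1.948 | 0.480 | 52% | 0.52 |
| 26/25 | 0.6 | 2.231 | 0.590 | 41% | 0.45 |
| 26/25 | 0.7 | 2.500 | 0.688 | 31% | 0.40 |

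For a true 0.3 SD difference with 73 analysed, power is 0.244 unadjusted and 0.352 at r = 0.6, so about 76% and 65% of trials would be non-significant. At an assumed SD of 4 to 6 points, the half-widths run from about 0.33 × 4 = 1.3 to 0.56 × 6 = 3.4 points.

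**Step 4: what a formal similarity claim would need.** Non-inferiority, one-sided 2.5%, 80% power, no true difference, no baseline adjustment: n per arm = 2 × ((1.960 + 0.842)/margin)². A margin of 0.5 SD needs 63 per arm (126 evaluable) and 0.3 SD needs 175. With 36.5 per arm, power is 57% and 25% respectively. Baseline adjustment helps: at r = 0.6 and 73 analysed, power is about 75% for 0.5 SD and 35% for 0.3 SD.

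**The case against.** A reader might infer that the protocol declares a non-significant result to be equivalence. It does not. The word non-significant is not used, the sentence is conditional Discussion prose and not a formal test, and an analysis plan that is not shown could define similarity. That stands. What remains is that the article attaches a positive conclusion to an undefined finding, and the only inferential framework it states is a difference test. An equivalence or non-inferiority margin would normally drive the sample size, and the stated sizing has none.

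A reader might also take 0.5 SD as the protocol's planning effect. It is not: f = 0.25 equals d = 0.5 only in a two-group one-way comparison, which does not give 98. Here 0.5 SD is only an illustration.

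The 58% figure should not be the headline. It describes unadjusted completers, whereas the plan is an intention-to-treat mixed model that keeps participants with missing data; the realistic figure lies within the range. Likewise, only with about 51 analysed and little adjustment (half-widths 0.52–0.56 SD) would an observed difference of zero fail to exclude 0.5 SD.

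Finally, the miss rates are per test. If similarity means that neither GAD-7 nor PHQ-9 differs, they overstate the risk. By simulation with 73 analysed, a 0.5 SD effect on each and correlation 0.5–0.7 between outcomes, both scales are non-significant at one time point in about 27–31% of trials unadjusted and 12–15% at r = 0.6. Across both scales and both time points, the latter falls to 5–9%. The risk therefore depends on how similarity is defined, which the article does not say.

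**Conclusion.** The point holds as a gap between a pre-stated conclusion and the evidence the design can supply. With 73 randomised, a true 0.5 SD advantage of high intensity would go undetected on one outcome at one time in about 16–44% of trials if all are analysed, and 31–58% if about 51 remain. The half-width of 0.33–0.56 SD leaves room for differences that could matter.

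This rests on 1:1 allocation, the stated attrition applying to this subset, a single-time-point approximation to the mixed model, and r between 0 and 0.7. The protocol's GAD-7 threshold of more than 5 points cannot stand in as a margin, because the article gives it for change over time and not for a difference between arms.

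The documents do not support saying that a missed difference is the likely result in every scenario, or that the trial is invalid. The interpretation should be corrected; the design and analysis model need not change.

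**What to change.** Replace the sentence under Principal Findings with a rule along these lines:

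- Report the low-minus-high difference in GAD-7 and PHQ-9 change from the planned mixed model at weeks 9 and 21, each with a 95% CI.
- Call low intensity non-inferior only if the CI bound on the side favouring high intensity excludes a justified margin that was fixed before results were seen. Call the two equivalent only if the whole CI lies within plus or minus that margin. These are different claims, and the rule should say which one is made.
- Otherwise call the comparison inconclusive.

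The Results section says that the trial results are already accepted for publication. If no margin was fixed beforehand, one should not be added now: report the estimate and CI only, and make no implementation claim based on similarity.

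The cost is one rule and a set of intervals from a model already planned. The downside is that the comparison will often read as inconclusive.

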### Limitations

Although the current trial is believed to contribute significantly to advancing the field of dMH interventions, the study is likely to have some limitations. Given the widely known high attrition rates in dMH treatment and the difficulties that people with depression and anxiety can face, such as avoidance and lack of motivation, participant recruitment and overall engagement may present a challenge. The study protocol has been designed with these considerations in mind, with the overall aim of reducing the impact of these challenges and furthering our knowledge about various support intensities of dMH treatment for anxiety and depression.

### Conclusions

This protocol outlines the first adaptive mixed methods clinical trial design investigating the efficacy of a 2-stage adaptive dMH intervention program incorporating both low-intensity and high-intensity therapist assistance delivered via video chat technology, compared with program-only support. This trial adds to the existing studies on dMH interventions and provides further understanding of participant and therapist experiences and satisfaction with video chat assessment and therapist assistance, along with therapist training and implementation experiences. Outcomes are expected to have implications for stepped care models and wide dissemination of dMH interventions for anxiety and depression.

## Appendix

Multimedia Appendix 1 Completed SPIRIT (Standard Protocol Items: Recommendations for Interventional Trials) checklist.

Multimedia Appendix 2 Cognitive Therapy Rating Scale manual.

## Abbreviations

AQol: Assessment of Quality of Life
BPSES: Bipolar Self-efficacy Scale
CMOTS: Client Motivation for Therapy Scale
CONSORT: Consolidated Standards of Reporting Trials
dMH: digital mental health
DSM-5: *Diagnostic and Statistical Manual for Mental Disorders, Fifth Edition*
GAD-7: Generalized Anxiety Disorder–7
MINI: Mini International Neuropsychiatric Interview
PHQ-9: Patient Health Questionnaire–9
SPIRIT: Standard Protocol Items: Recommendations for Interventional Trials
WAI-S: Working Alliance Inventory–Short
